### 2.8. Ethical Considerations

The study protocol was approved by the relevant Ethics Committee (RS1851/23, 2773, version v.0) and was recorded on ClinicalTrial.gov (identifier number NCT06254196, last update posted on 3 June 2024). Including patients in the project will be preceded by acquiring specific written informed consent. By signing the informed consent form, patients will formally agree to adhere to the procedures of the project study, thereby authorizing the authors to collect and analyse the data and disseminate the results to the scientific community. The data will be analysed in an aggregated and pseudo-anonymous form, and participants can only be identified by the research team. Moreover, data will be collected, stored, used, processed and transmitted in compliance with current legislation, guaranteeing its quality, integrity, security, availability and traceability following the original protocol. Possible changes to the protocol will be submitted to the committee for an appropriate opinion.

## 3. Expected Results

The results of this RCT could highlight the impact of an increased nursing contribution and telenursing interventions on SCNs [18,19] and cancer care.

The study protocol aims to assess the impact of a telenursing intervention in patients with lung cancer and melanoma at the first prescription of TT. In particular, this study aims to assess the impact of telenursing interventions on the SCNs [18,19] after one month of treatment (primary outcome) and improve the clinical pathways of patients with melanoma and lung cancer on TT. Regarding the safety of care, telenursing interventions aim to enhance clinical practice through a more outstanding nursing contribution with remote care. Furthermore, this study’s results could allow nurses to offer a more significant contribution within multidisciplinary teams in the therapeutic pathways of patients with cancer, as suggested by the previous literature, and improve their skills in this regard [29]. The importance of nurses’ contribution to remote care is inherent in its potential developments, present and future, for the discipline, the healthcare organizations and the community. In particular, as suggested by previous studies [32], this clinical trial could highlight, even in telenursing, the importance of the nurse–patient relationship, based on mutual trust, communication, common values and health objectives.

### 3.1. Strengths and Limitations of the Work

To the best of the authors’ knowledge, this is the first RCT to assess the impact of telenursing interventions on the clinical pathway of patients with melanoma and lung cancer on TT. In particular, it could be helpful to assess the effects of a broader nursing contribution on the SCNs [18,19] at one month (primary outcome), the main AEs, therapeutic adherence [24,25], QoL [20,21], system usability and satisfaction [22,23], performance status [26] and PROs at one, three and six months (secondary outcomes).

The authors are aware of the limitations of the study. First, the small sample size and the two cancer types enrolled (lung cancer and melanoma) should be considered. Furthermore, the lack of stratification by age and pathology may not allow the authors to capture differences or risk classes to consider through inference on a larger sample. The enrolment of patients in the exclusive TT does not allow for the inclusion of patients who probably could benefit from the interventions in the study. However, to reduce the weight of the limitations of the present study protocol, the authors trust in the methodological rigour of the study design.

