To promote the generalisability of the results, considering their incidence and common therapeutic approaches, patients with melanoma and lung cancer were included in this study [16,17].

Furthermore, due to the prevalence and the high burden of lung cancer and melanoma in patients on TT, comparing a telenursing intervention with standard care could highlight its efficacy in cancer care.

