### 2.2. Study Setting and Sampling

The RCT will be performed in a national cancer centre starting on 1 April 2024. A nursing team will lead the project in collaboration with medical oncologists. The sample size calculation was performed on the primary outcome, the SCNs scale [18,19] measured one month after treatment, considering possible losses to follow-up (drop-out rate). The study by Ebrahimabadi [18] allowed the researchers to hypothesise the following:A mean score and its relative standard deviation (SD) in the intervention group equal to 81.53 (±13.2),A mean score and its relative SD in the control group equal to 103.5 (±21.96), with a statistical power of 90% and a significance level α = 0.05, while a two-tailed Student’s *t*-test estimated an overall size of 32 patients, 16 for each group. Given the mean score reported in the hypothesis system, we obtain an effect size equal to 1.21. Considering a drop-out rate of 20%, we will enrol a total sample of 40 patients. The software NCSS PASS v.11.0 was used to assess the minimum size. Evaluation of the statistical tests will be carried out by an expert statistician.

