
After nurses have obtained the informed consent, 40 patients with melanoma and lung cancer (20 in each group) will be randomised into the IA (telenursing intervention added to clinical practice) or the CA (clinical practice). To allow for comparison, at baseline (T0) before the randomisation, patients from both groups will complete the tools shown in Table 1 in paper format. Additionally, patients involved in the study will use the study tools according to the timelines described in Table 1 at T1 (30 days), T2 (90 days), and T3 (180 days). Regarding the practice procedures, monthly telenursing interventions will be provided every 30 days, on dates agreed in advance with patients. However, patients will be able to communicate with the nursing staff via short messages or by telephone at any time of the day, between 8 a.m. and 2 p.m. An unplanned nursing intervention can be useful in case of patient doubts or problems related to therapeutic adherence (dosage errors, forgotten or double doses, etc.), onset of new side effects, sudden alterations in vital signs, etc. In addition, in view of the daily questionnaire filled out by patients (Table 1), nursing staff will implement additional interventions as needed, remotely or in person.

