### 2.5. Fidelity of Intervention and Randomisation

Nurses will prevent and manage both groups of patients’ toxicities and needs according to good clinical practice [31], in collaboration with the oncologists.

The random sequence of eligible patients in the CA and the IA will be 1:1. The assignment list will be generated by special software before the study starts, and it will be unknown to the nurses and the oncologists. Due to the nature of the interventions, the patients and healthcare professionals will not be blinded. In case of system dysfunctions or desire to leave the study, all the patients will be followed according to the current clinical practice by healthcare teams.

Patients may drop out of the study at any time without affecting their care pathways, which will continue to be provided according to current clinical practice. At the same time, patients who do not adhere to the study procedures may be excluded from the study after 15 days of missing data.

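### Two cancers are pooled in 40 patients without stratification by tumour type, leaving about a 24–34% chance of a 20-point gap in tumour share that the named tests do not adjust for

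*Protocol article*

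**What the plan says.** Section 2.4 states that "40 patients with melanoma and lung cancer (20 in each group) will be randomised into the IA" or the control arm. Section 2.5 adds that "The random sequence of eligible patients in the CA and the IA will be 1:1" and that "The assignment list will be generated by special software before the study starts"; it mentions no strata and no blocks. Section 3.1 confirms that the absence of strata is a decision, because it lists as a limitation that "the lack of stratification by age and pathology may not allow the authors to capture differences or risk classes". The same paragraph says that "the small sample size and the two cancer types enrolled (lung cancer and melanoma) should be considered". The Introduction gives the reason for enrolling both diseases: "To promote the generalisability of the results, considering their incidence and common therapeutic approaches, patients with melanoma and lung cancer were included".

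Section 2.7 compares continuous outcomes between arms with Student's t test or the Mann–Whitney U test, and categorical ones with chi-square or Fisher's exact test. No covariate is named. The protocol gives neither the expected lung/melanoma split nor any difference in supportive care needs between the two cancers.

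**The concern.** Diagnosis is an eligibility criterion (Section 2.3), so tumour type is known before every randomisation. With 20 patients per arm, chance alone can leave one arm with clearly more lung cancer than the other. If supportive care needs differ between the two cancers, part of the observed one-month difference in such a trial would reflect the tumour mix. A reader would then find it harder to judge how much is due to telenursing and whether the result applies to both cancers, which is the stated purpose of pooling them. Even in a balanced trial, leaving a prognostic factor out of the analysis leaves its variation in the error term.

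Section 3.1 presents the lack of stratification as a limit on identifying subgroups or risk classes. It does not mention balance between arms, and its only mitigation is a general appeal to the rigour of the design.

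**Working it through.** **Inputs from the protocol.** N = 40, 20 per arm (Section 2.4). Means 81.53 (SD 13.2) and 103.5 (SD 21.96), power 90%, two-sided α = 0.05, 16 evaluable per arm, 20% drop-out (Section 2.2).

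**Assumptions, because the protocol gives no figure.** Tumour mix from 20/80 to 50/50 (which cancer is the minority makes no difference); a difference in mean supportive care needs between the cancers of 5, 10 or 20 points.

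**1. The plan's own sample size.** Difference = 103.5 − 81.53 = 21.97. Pooled SD = √((13.2² + 21.96²)/2) = √328.24 = 18.12. Effect size = 21.97/18.12 = 1.21, as stated. The noncentral t distribution gives power 0.893 at 15 per arm and 0.913 at 16, so 16 per arm is right. 32/0.80 = 40. The sample size reproduces.

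**2. Chance of imbalance.** Let K of the 40 patients have one cancer and X be the number of these in one arm of 20. Without stratification X is hypergeometric (40, K, 20), and the gap in tumour share is |2X − K|/20.

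| Mix (K of 40) | gap ≥ 10 points | gap ≥ 20 points | gap ≥ 30 points |
|---|---|---|---|
| 20/80 (8) | 70% | 24% | 4% |
| 30/70 (12) | 73% | 30% | 8% |
| 50/50 (20) | 75% | 34% | 11% |

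At 50/50, a 20-point gap is 12 versus 8 patients. The table assumes exactly 20 per arm. If the list were a simple coin flip, the 50/50 figures would be 27% (≥ 20 points) and 8% (≥ 30 points).

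**3. Shift in the estimate.** Shift = gap × tumour difference.

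- 20-point gap, 10-point difference: 0.20 × 10 = 2.0 points, which is 2.0/21.97 = 9% of the planned difference.
- 30-point gap, 20-point difference: 0.30 × 20 = 6.0 points, or 6.0/21.97 = 27%.

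The standard error at 16 per arm is 18.12 × √(2/16) = 6.4, so these shifts are about 0.3 and 0.9 standard errors.

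**4. Type I error.** Simulation with no treatment effect, 20 per arm, 50/50 mix, total SD 18.12, unadjusted test:

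| Assumed tumour difference | all randomisations | only those with gap ≥ 30 points |
|---|---|---|
| 5 points | 4.5% | 4.9% |
| 10 points | 4.7% | 7.8% |
| 20 points | 4.8% | 16.8% |

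The last column applies to about 12% of the simulated trials.

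**5. Precision.** At a 50/50 mix, a tumour difference g adds g²/4 to the variance. For g = 10 this is 25 of 328.24 (8%), and for g = 20 it is 100 of 328.24 (30%). Adjustment removes that part. Simulated power at 16 per arm:

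| Assumed tumour difference | unadjusted | adjusted for tumour type |
|---|---|---|
| 5 points | 91.4% | 91.0% |
| 10 points | 91.4% | 92.5% |
| 20 points | 91.0% | 97.5% |

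**6. Effect of stratifying.** Within a stratum, permuted blocks hold the difference between arms to at most half a block. With blocks of 4 (an assumed size) that is 2 patients, or about 2/20 = 10 points in tumour share. N stays at 40.

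**The case against.** The strongest reply is that nothing here is an error. Chance imbalance is part of the sampling variation that the test already allows for, and step 4 bears this out: over all randomisations the type I error stays just under 5%. The authors declare the limitation openly. The Introduction justifies pooling by therapeutic approaches that the two cancers share. Section 1.2 gives one symptom list for all patients and assigns no symptom to either cancer, so the documents do not show that supportive care needs differ by tumour type. A moderate case (20-point gap, 10-point difference) shifts the estimate by only about 0.3 standard errors. Covariate adjustment and block details are often left to a full protocol or analysis plan, which is not shown. Stratification also has a price: the split may not be exactly 20/20, and Section 2.8 sends protocol changes to the ethics committee.

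Most of this stands and limits the claim. It does not remove the point. The absence of stratification by pathology is stated in the article, so it is not a detail held over for another document. Declaring a limitation does not reduce it when a remedy is available that costs no patients.

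A reader might infer that a sizeable imbalance is likely. The figures do not support that: only a gap of 10 points (two patients) is more likely than not, and a gap of 20 points or more is a risk of roughly one in four to one in three. A reader might also infer that tumour type would be confounded with the telenursing effect. Randomisation prevents this in general. A distortion needs both an imbalanced allocation and a tumour type that predicts the outcome, and the documents give no figure for the second.

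**Conclusion.** The point holds as an avoidable weakness of the design. It does not invalidate the trial. As described, neither the allocation nor the named tests take account of tumour type. With exactly 20 per arm and a mix between 20/80 and 50/50, the chance of a gap in tumour share is about 24–34% for 20 points or more and about 4–11% for 30 points or more. The overall type I error is not inflated.

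The consequence for an individual result depends on an unknown. It is negligible if the cancers differ by about 5 points in supportive care needs, modest at 10, and material only when a difference near 20 points meets a gap of 30 points or more. The tumour mix, the tumour differences and the block size are assumptions of this review. An analysis plan that already adjusts for tumour type would answer the analysis half of the point.

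**What to change.** 1. Make tumour type (lung cancer, melanoma) a prespecified factor in the primary comparison at one month, for example a linear model with terms for arm and tumour type. If the rank test is used, take its version stratified by tumour type (van Elteren). This works whether or not enrolment has begun, provided it is fixed before outcomes are compared by arm.

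2. If the list is not yet in use, generate it in two strata with permuted blocks of varied, concealed size. Variation matters because patients and staff are not blinded and a fixed block could be guessed. Whether this step is still open is uncertain, since Section 2.6 has the first patient entering after 15 June 2024.

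3. Do not add age as a stratum; further strata would be too sparse in 40 patients.

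**Cost.** No extra patients, and power is kept or raised (step 5). Each stratum may end in an incomplete block: with blocks of 4 the two strata together could leave at worst 22 versus 18, and larger blocks somewhat more. The list would have to be regenerated by the trial-support staff who randomise (Table 2), and the change must be submitted to the ethics committee under Section 2.8.

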### 3.2. Recommendations for Further Research and Practice

The results of the present study protocol should undoubtedly be tested on more extensive and heterogeneous samples and populations to assess the effectiveness and reliability in patients with cancer on TT.

## 4. Conclusions

Telenursing interventions could significantly challenge nurses in improving cancer care outcomes [11]. Remote interactions promote patient–nurse coaching interventions to improve cancer patients’ self-care and problem-solving skills during chemotherapy. Nursing alerts for severe toxicities can enable early interventions to manage treatment-related issues, reducing interruptions and improving clinical outcomes [33]. Continuous monitoring could also enhance communication with the care team and highlight the reasons for non-adherence among cancer patients. The expected results could be used in implementing patient-centred telenursing interventions to be tested on larger populations affected by other treatments and illnesses.

## Figures and Tables

**Table 1 mps-07-00078-t001:** Outcomes and tools.

Time	User	Outcomes	Tools (Citation)
Monthly	Nurse/Clinician	Adverse events	Common Terminology Criteria for Adverse Events
T0	Nurse	Clinical-anamnestic-demographic data	Registry card
Daily	Patients	Vital signs and main symptoms from patient-reported outcomes	Patient-reported outcomes
T0, T1, T2, T3	Patients	Patient-reported outcomes	Patient-reported outcomes
T0, T1, T2, T3	Nurse/Clinician	Performance status	Karnofsky performance status
T0, T1, T2, T3	Patients	Quality of life	Quality of Life SF-36
T1, T2, T3	Patients	System satisfaction and usability	SUS—System Usability Scale
T0, T1, T2, T3	Patients	Supportive care needs	Supportive care needs
T0, T1, T2, T3	Patients	Therapeutic adherence	MARS-5I

T0: baseline; T1: 30 days; T2: 90 days; T3: 180 days; SF: short form; MARS-5I: Medication Adherence Report Scale Italian.

**Table 2 mps-07-00078-t002:** Participants’ timeline.

Timeline (People Involved)	T0 Baseline	T1 Month 1	Month 2	T2 Month 3	Month 4	Month 5	T3 Month 6
			**INTERVENTION ARM**				
enrolment (nurses and oncologists)	√						
randomisation (staff MSCT)	√						
follow-up visits (nurses and oncologists)		√	√	√	√	√	√
telenursing interventions (nurses)	√	√	√	√	√	√	√
monthly measurement (patients, nurses and oncologists)	√	√	√	√	√	√	√
			**CONTROL ARM**				
enrollment (nurses and oncologists)	√						
randomisation (staff MSCT)	√						
follow-up visits (oncologists)		√	√	√	√	√	√
monthly measurement (patients and oncologists)	√	√	√	√	√	√	√

MSCT: Monitoring and Supporting Clinical Trials.

## Data Availability

The datasets generated and analysed during the current study will be available from the corresponding author upon reasonable request.
